# Acupuncture treatment for insulin sensitivity of women with polycystic ovary syndrome and insulin resistance: a study protocol for a randomized controlled trial

**DOI:** 10.1186/s13063-017-1854-2

**Published:** 2017-03-09

**Keywords:** Acupuncture, Metformin, Sham acupuncture, Polycystic ovary syndrome, Insulin resistance

## Abstract

**Background:**

Our prospective pilot study of acupuncture affecting insulin sensitivity on polycystic ovary syndrome (PCOS) combined with insulin resistance (IR) showed that acupuncture had a significant effect on improving the insulin sensitivity of PCOS. But there is still no randomized controlled trial to determine the effect of acupuncture on the insulin sensitivity in women with PCOS and IR. In this article, we present the protocol of a randomized controlled trial to compare the effect of true acupuncture on the insulin sensitivity of these patients compared with metformin and sham acupuncture. Acupuncture may be an effective therapeutic alternative that is superior to metformin and sham acupuncture in improving the insulin sensitivity of PCOS combined with IR.

**Methods:**

This study is a multi-center, controlled, double-blind, and randomized clinical trial aiming to evaluate the effect of acupuncture on the insulin sensitivity in PCOS combined with IR. In total 342 patients diagnosed with PCOS and IR will be enrolled. Participants will be randomized to one of the three groups: (1) true acupuncture + metformin placebo; (2) sham acupuncture + metformin, and (3) sham acupuncture + metformin placebo. Participants and assessors will be blinded. The acupuncture intervention will be given 3 days per week for a total of 48 treatment sessions during 4 months. Metformin (0.5 g per pill) or placebo will be given, three times per day, and for 4 months.

Primary outcome measures are changes in homeostasis model assessment of insulin resistance (HOMA-IR) and improvement rate of HOMA-IR by oral glucose tolerance test (OGTT) and insulin releasing test (Ins). Secondary outcome measures are homeostasis model assessment-β (HOMA-β), area under the curve for glucose and insulin, frequency of regular menstrual cycles and ovulation, body composition, metabolic profile, hormonal profile, questionnaires, side effect profile, and expectation and credibility of treatment.

Outcome measures are collected at baseline, at the end of treatments, and 3 months after the last acupuncture treatment. On completion of the screening visit, randomization will be conducted using a central randomization system.

**Discussion:**

This study will investigate the effects of acupuncture on the insulin sensitivity of PCOS and IR women compared with metformin and sham acupuncture. We will test whether true acupuncture with needles placed in skeletal muscles and stimulated manually and by electrical stimulation is more effective than metformin and sham acupuncture with superficial needle placement with no manual or electrical stimulation in improving the insulin sensitivity in PCOS women with IR.

**Trial registration:**

ClinicalTrials.gov, NCT02491333; Chinese Clinical Trial Registry, ChiCTR-ICR-15006639. Registered on 24 June 2015.

**Electronic supplementary material:**

The online version of this article (doi:10.1186/s13063-017-1854-2) contains supplementary material, which is available to authorized users.

## Background

Polycystic ovary syndrome (PCOS) is one of the most common endocrine disorders in reproductive age women. It is characterized by chronic anovulation and hyperandrogenism and is often accompanied by obesity and insulin resistance (IR) as IR is present in nearly 40% of PCOS [1]. In addition, IR, hyperinsulinemia, and dyslipidemia worsen with aging, and the risk of miscarriage is three times higher than in healthy women [2]. They are also at an increased risk of pregnancy complications such as impaired glucose tolerance, gestational diabetes mellitus, pregnancy-induced hypertension and preeclampsia, and small for gestational age children [2]. It may affect general health and the quality of life. Both hyperandrogenism and IR contribute to the pathogenesis of many aspects of PCOS [3, 4].

IR in PCOS results from hyperinsulinemia and defects in the insulin signaling pathway. Further, high concentrations of insulin reduce circulating levels of sex hormone binding globulin (SHBG) and increase levels of free testosterone, and the latter leads to menstrual disturbance, development of ovarian cysts, hirsutism, and anovulatory infertility [5]. IR leads to a higher risk of impaired glucose, type 2 diabetes, dyslipidemia, atherosclerosis, and vascular disease [6].

The first-line treatment for overweight or obese women with PCOS is modification of diet and lifestyle. This confirmed that the benefit of improved ovulation and live birth with delayed infertility treatment with clomiphene citrate when preceded by lifestyle modification with weight loss was superior to immediate treatment [7], but for many subjects it is not easy to sustain [8]. Treatments of IR with insulin-sensitizing agents have been used in women with PCOS [9]. Metformin, an insulin-sensitizing agent known to decrease hepatic glucose production via a transient inhibition of the mitochondrial respiratory-chain complex 1 and an activation of the AMP-activated protein kinase (a cellular metabolic sensor [10]), improves irregular menstrual cycles in women with PCOS whether IR is present or not [11]. Nevertheless, it is not effective in treating hirsutism, acne, or anovulatory infertility [12]. It also has side effects such as gastrointestinal irritation (diarrhea and nausea) and lactic acidosis, which is rare but serious [13]. In addition, metformin is not recommended for patients with kidney, lung, liver, and heart disease or on a low-carbohydrate diet [14]. Other common insulin-sensitizing agents are thiazolidinediones, including troglitazone (which is no longer available for clinical use), rosiglitazone, and pioglitazone [15]. However, rosiglitazone may result in cardiovascular diseases [16], and pioglitazone may increase the risk of bladder cancer [17]. Both may double the risk of bone fractures [18]. Given that current pharmacological treatments have such side effects, there is an urgent need to find a better and safer therapy for IR in PCOS women.

As an integrated part of Traditional Chinese Medicine and a relatively safe treatment [19], acupuncture treatment for PCOS has gained increasing attention in recent years. The effect of acupuncture is most likely mediated via activation of sensory nerve fibers, which in turn modulate the sympathetic activity to the ovaries and in the central nervous system [20, 21]. A review found that acupuncture can correct various metabolic disorders contributing to the development of IR, such as hyperglycemia, overweight, hyperphagia, hyperlipidemia, inflammation, altered activity of the sympathetic nervous system, and insulin signal defect [22]. Thus, acupuncture may have the potential to improve insulin sensitivity [22]. Other findings suggest that electrical acupuncture stimulation affects more functional signaling pathways related to insulin sensitivity, while manual stimulation of acupuncture needles has a greater effect on glucose tolerance [23]. Furthermore, in female insulin-resistant rats both electrical and manual acupuncture stimulation enhances insulin sensitivity via activation of sensory afferents [24]. Our prospective pilot study (ClinicalTrials.gov NCT02026323) [25] of acupuncture affecting the insulin sensitivity in 81 cases of women with PCOS with IR showed that acupuncture has a significant effect on improving the insulin sensitivity in these patients. But there is still no randomized controlled trial to determine the effect of acupuncture on insulin sensitivity in women with PCOS combined with IR.

Thus, we present the protocol of a randomized controlled trial to investigate the effects of acupuncture on the insulin sensitivity of women with PCOS combined with IR. We hypothesize that true acupuncture is superior to metformin and sham acupuncture in improving insulin sensitivity.

### Objectives

The primary objective of this randomized controlled trial is to evaluate the hypothesis that true acupuncture + metformin placebo (group 1) improves insulin sensitivity, as measured by changes in the homeostasis model assessment of insulin resistance (HOMA-IR), more effectively than sham acupuncture + metformin (group 2) and sham acupuncture + metformin placebo (group 3) in women with PCOS and IR. Secondary objectives include changes in HOMA-β (islet β-cell function), C-peptide index, the insulin response to glucose calculated from the oral glucose tolerance test (OGTT) and insulin releasing test (Ins), frequency of the regular menstrual cycle and ovulation, circulating sex steroids, lipid profile, health-related quality of life and symptoms of anxiety and depression, side effects, and credibility.

## Methods

### Overview

This is a randomized controlled trial to determine the effect of true acupuncture + metformin placebo for the improvement of insulin sensitivity in women with PCOS and IR compared with sham acupuncture + metformin and sham acupuncture + metformin placebo. The design of this study is compliant with the Consolidated Standards of Reporting Trials (CONSORT) guidelines [26] and with the Standard Protocol Items: Recommendations for Interventional Trials (SPIRIT) statement 2013 [27] [see Additional file 1].

### Patients and enrollment

Women with PCOS and IR will be recruited from the Department of Traditional Chinese Medicine in the First Affiliated Hospital of Guangzhou Medical University, Xuzhou Maternity & Child Health Hospital, Dalian Municipal Women and Children’s Medical Center, Guangdong Women and Children’s Hospital, *and* Hexian Memorial Affiliated Hospital of Southern Medical University if they meet the inclusion criteria and do not have any exclusion criteria. Eligible subjects will be approached and sign the consent form after detailed explanation of the study design and comprehensive counseling (see the flow diagram in Fig. 1).

**Fig. 1 Fig1:**
[figure not shown]
CONSORT flow diagram of the study. *PCOS* polycystic ovary syndrome; *HOMA* homeostatic model assessment; *IR* insulin resistance; *AUC* area under the curve

#### Inclusion Criteria

Chinese women aged from 18 to 40 years.﻿Body mass index ﻿(BMI) ≥18.5 kg/m^2^.Confirmed diagnosis of PCOS according to the Rotterdam criteria in 2003 including at least two of the following three features: (1) oligo- (an intermenstrual interval >35 days or <8 cycles in the past year) or amenorrhea (an intermenstrual interval >90 days), and/or (2) polycystic ovarian morphology, i.e., presence of >12 antral follicles (≤9 mm) and/or ovarian volume >10 ml on ultrasonography scanning, and/or (3) clinical and/or biochemical hyperandrogenism. Clinical hyperandrogenism on the Chinese Mainland is defined as a Ferriman-Gallwey (FG) score ≥5 [28]; biochemical hyperandrogenism is total testosterone (T) >2.6 nmol/l and free testosterone ≥6.0 pg/ml [29].Presence of IR as defined by the homeostatic model assessment—HOMA-IR: [fasting insulin (μU/ml) × fasting glucose (mmol/l)] / 22.5). A value ≥2.14 is considered to be indicative of IR [30].No immediate fertility wish and willingness to use barrier contraceptive methods for 7 months.Willingness to sign the consent form.

#### Exclusion Criteria

Exclusion of other endocrine disorders:Uncorrected thyroid disease (defined as thyroid stimulating hormone (TSH) < 0.2 mIU/ml or >5.5 mIU/ml, triiodothyronine (T3) < 1.4 nmol/l or >2.2 nmol/l, and free thyroxine (T4)  < 10 pmol/l or >23 pmol/l). A normal level within the last year is adequate for entry.Poorly controlled type I or type II diabetes (defined as a glycosylated hemoglobin (HbA1c) level >7.0%) or patients receiving antidiabetic medications such as insulin, thiazolidinediones, acarbose, or sulfonylureas likely to confound the effects of the study medication; patients currently receiving metformin XR (extended release) for a diagnosis of type I or type II diabetes or for PCOS are also excluded.Cushing’s syndrome (defined as an archetype of metabolism syndrome. High glucocorticoid levels lead to muscle, liver, and adipocyte insulin resistance; 17-hydorxycorticosteroids >55 umol/24 h or urinary-free cortisol >304 nmol/24 h).Congenital adrenal hyperplasia (defined as patients with known 21-hydroxylasedeficiency or other enzyme deficiency leading to the phenotype of congenital adrenal hyperplasia; 17-oh progesterone >10 ng/ml in adrenocorticotropic hormone 1-24 h excited test (after 60 min).Suspected androgen-secreting adrenal or ovarian tumor.
Use of hormonal or other medication including Chinese herbal prescriptions, which may affect the outcome of the last 2 months.Receiving acupuncture in the past 2 months.Within 6 weeks of pregnancy.Post-abortion or postpartum within the past 6 weeks.Breastfeeding within the last 4 months.Not willing to give written consent to the study.Having a bariatric surgery procedure within the past 12 months or being in a period of acute weight loss.Additional exclusion criteria include:Patients on oral contraceptives, depot progestin, or hormonal implants (including Implanon). A 2-month washout period will be required prior to screening for patients on these agents. Longer washouts may be necessary for certain depot contraceptive forms or implants, especially where the implants are still in place. A 1-month washout will be required for patients on oral cyclic progestin.Heart disease.Patients with a history of or suspected cervical carcinoma, endometrial carcinoma, or breast carcinoma.Patients enrolled in other studies that require medications.Patients taking longer than a 1-month break during the protocol should not be enrolled.

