### Study-specific visits and procedures

Patients will attend five visits, including the screening visit, baseline measurements, treatment visit, after-treatment measurements, and follow-up measurements. Months indicate when each specific measurement takes place. Adverse events and concomitant medications will be recorded during every visit. The overview of study visits is shown in Table 3.

**Table 3 Tab3:** Overview of study visits

	Screening visit	Baseline visit	Month				Follow-up after 4 months of treatment	End of treatment visit 3 months after the last acupuncture treatment
			1st	2nd	3rd	4th		
OGTT and Ins		√					√	√
Body composition (weight, height, waist circumference, hip circumference, FG/acne)	√	√	√	√	√	√	√	√
Menstrual cycle diary	√	√	√	√	√	√	√	√
Fasting blood samples for FGLU, FINS, HbA1c, C-peptide, TSH, T3, free T4	√							
Fasting blood samples for FSH, LH, SHBG, T, E2, PRL		√					√	√
Fasting blood samples for ApoA1,ApoB, TC, TG, HDL-C, LDL-C, BRT, renal and liver profile		√					√	√
Transvaginal or transrectal ultrasound	√						√	√
Questionnaires		√					√	√

*Apoa1* apolipoprotein A1, *ApoB* apolipoprotein B, *BRT* blood routine test, *E2* estradiol, *FG* Ferriman-Gallwey score, ﻿*FGLU* f﻿asting blood glucose*, FINS* Fasting insulin, *FSH* follicle-stimulating hormone, *HbA1c* glycosylated hemoglobin, *HDL-C* high density lipoprotein, *LDL-C* low density lipoprotein, *LH* luteinizing hormone, *PRL* prolactin, *SHBG* sex hormone-binding globulin, *T* total testosterone, *TC* total cholesterol, *TG* triglyceride, *TSH* thyroid stimulating hormone, *T3* triiodothyronine, *T4 *thyroxine, *OGTT* oral glucose tolerance test, *Ins* insulin-releasing test

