#### Check urine pregnancy test

##### Fasting blood samples to exclude other endocrine disorders

Fasting (at least 4 h) blood samples are taken to exclude any endocrine disorders:

Fasting glucose, fasting insulin, HbA1C (>7%), C-peptide, TSH (<0.2 mIU/ml or >5.5 mIU/ml), T3 (<1.4 nmol/l or >2.2 nmol/l), and free T4 (<10 pmol/l or >23 pmol/l).

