#### Progestin withdrawal

Provide progestin prescription to induce withdrawal bleeding, with instructions to begin medication once eligibility has been determined.

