### Baseline visit

After the screening visit, if a woman fulfills inclusion criteria and has signed the informed consent form, she will be assigned to the baseline visit. The baseline visit takes place day 2–5 of a spontaneous period or after a withdrawal bleeding after an overnight fast.

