#### Laboratory Examination

Blood will be collected. Part of it will be stored, and the remainder is used for determination of DNA and sphingolipid levels.
*Circulating sex steroids:* Fasting serum levels of follicle-stimulating hormone (FSH), luteinizing hormone (LH), estradiol (E2), prolactin (PRL) and T, and sex hormone binding globulin (SHBG).
*Lipid profile:* Triglycerides (TG), total cholesterol (TC), high-density lipoprotein (HDL-C), low-density lipoprotein (LDL-C), apolipoprotein A1 (ApoA1), apolipoprotein B (ApoB), blood routine test﻿(BRT), and renal and liver profiles.
*Glucose homeostasis and insulin sensitivity:* The OGTT and Ins with 75 g glucose. Blood samples will be obtained to measure plasma glucose, serum insulin, and C-peptide at 0, 60, and 120 min during the OGTT and Ins.

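### Of the four organ diseases in which the protocol advises against metformin, only heart disease is an exclusion, and the renal and liver profile is first drawn after eligibility and randomization

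*Protocol article*

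**What the plan says.** The Background, arguing for an alternative to existing drugs, states that "metformin is not recommended for patients with kidney, lung, liver, and heart disease or on a low-carbohydrate diet". It also lists among metformin's side effects "lactic acidosis, which is rare but serious".

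Exclusion Criteria gives numerical limits for thyroid function, HbA1c, cortisol and 17-OH progesterone, washout periods for several hormonal products, and short medical items such as "Heart disease.Patients with a history of or suspected cervical carcinoma". Kidney and lung disease do not appear. The liver is mentioned only in the description of Cushing's syndrome. The Inclusion Criteria contain no renal, hepatic or pulmonary condition.

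The screening bloods are taken to rule out endocrine disorders and begin "Fasting glucose, fasting insulin, HbA1C (>7%), C-peptide, TSH"; T3 and free T4 complete the list. After screening, "if a woman fulfills inclusion criteria and has signed the informed consent form, she will be assigned to the baseline visit". The progestin prescription at screening comes "with instructions to begin medication once eligibility has been determined", so eligibility is meant to be settled before the baseline visit. The Abstract (Methods) places central randomization at the completion of the screening visit.

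The baseline Laboratory Examination adds, at the end of the lipid item, "and renal and liver profiles". In Table 3 the row "Fasting blood samples for ApoA1,ApoB, TC, TG, HDL-C, LDL-C, BRT, renal and liver profile" is ticked at baseline, after 4 months of treatment, and 3 months after the last acupuncture session. It is not ticked at screening or in months 1 to 4. The section Metformin and placebo starts tablets 2 days after the baseline visit.

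**The concern.** The article itself names the patients in whom it advises against metformin, and then gives metformin to one of three arms under entry rules that carry over one of the four organ diseases. The eligibility list is long and specific, so a reader would expect the other three to be there if they were meant to apply.

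The order of events adds to this. The one scheduled test that could reveal kidney or liver impairment comes after the entry decision and, on the Abstract's wording, after allocation. Acting on an abnormal result would then mean stopping or withholding tablets in a woman already randomized. Site investigators are blinded to metformin or placebo, so they could not restrict that step to the women who are actually on metformin.

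At stake is participant safety in the sham acupuncture + metformin arm. Sample size, error rates and the primary comparison are not in question.

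**Working it through.** No figure in the plan depends on this point, so there is nothing to reproduce. The check sets the sections side by side and then sizes the exposure.

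**Background cautions against entry rules**

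| Condition named in the Background | In Exclusion Criteria? | Test at screening? | Scheduled test before dosing? |
|---|---|---|---|
| Heart disease | Yes | Complete physical examination only | No specific test |
| Kidney disease | No | None | Renal profile at baseline |
| Liver disease | No (liver mentioned only under Cushing's syndrome) | None | Liver profile at baseline |
| Lung disease | No | Complete physical examination only | No specific test |

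Count: 1 of 4 organ diseases is an exclusion and 3 of 4 are not. The number of printed entry criteria that use the renal or liver profile is 0. (The Background's diet caution is not pursued here.)

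**Order of events**

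1. Screening visit: endocrine bloods, physical examination, ultrasound; eligibility determined.
2. Randomization on completion of screening (Abstract, Methods).
3. Baseline visit: first renal and liver profile.
4. Tablets start 2 days after baseline.
5. Next scheduled renal and liver profile: the visit after 4 months of treatment (Table 3).

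The first renal or liver result therefore arrives before dosing but after allocation.

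**Exposure in the metformin arm**

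- Daily dose (Metformin and placebo): 3 × 0.5 g = 1.5 g.
- Kit (Randomization and patient allocation): 336 tablets / 3 per day = 112 days = 16 weeks.
- Total at full dose: 336 × 0.5 g = 168 g.

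These figures describe drug supply. They are not a measure of risk.

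**Women an amendment could still reach**

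- Planned 342, of whom 114 were randomized by the end of December 2016 (Trial status): 342 − 114 = 228.
- With 1:1:1 allocation, 228 / 3 = 76 to metformin.

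Both are upper limits, because recruitment continued after that date. The documents give no prevalence of kidney, liver or lung disease in this population, and none is assumed.

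**The case against.** The strongest reply is that this is mostly an absence in a condensed article. The full protocol is not shown, and it may hold further exclusions and a rule for reviewing baseline safety bloods. The detailed limits in the printed list concern endocrine disorders, while the general medical items are brief labels, so the detail does not prove that the list is complete. This is a fair reason for moderate confidence. It does not remove the point, because the article prints one of its own four cautions as an exclusion and leaves out the other three, and it prints a visit table that places the test after eligibility. No missing laboratory limit is held against the article.

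Second, the Background sentence is motivation and not an eligibility rule. It gives no severity, and lung disease taken literally would cover mild asthma. This stands: the documents do not settle that every lung condition should exclude a woman.

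Third, there are safeguards: a complete physical examination at screening, monthly examinations, adverse events recorded at every visit, quarterly DSMB review with immediate review of serious events, and dose reduction for adverse effects, where nausea and dizziness are given only as examples. They limit harm, but except for the screening examination they act after allocation.

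A reader might go further and infer that a woman with silent renal or liver impairment would take the whole 16-week course before anyone found out. The documents do not support this. Every woman has a renal and liver profile at baseline, 2 days before the first tablet, and impairment present at entry would normally show there. That inference needs the result to be unread or ignored. The article is silent on how the result is used, and silence is not evidence that it goes unused.

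**Conclusion.** The point holds in limited form. The printed entry rules allow a woman with known kidney or liver disease, or significant lung disease, to be randomized to metformin 1.5 g/day, although the article's own text advises against the drug in such women. An abnormal baseline renal or liver result can be acted on only after she has been allocated.

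This rests on three readings: that the printed exclusion list is the one in force, that randomization follows screening as the Abstract says, and that no rule outside the article ties entry to the profile. If the full protocol already has these exclusions and a review before randomization, the sponsor can close the point by saying so.

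The number of women affected is unknown and probably small at ages 18 to 40. This is a minor to moderate safety point, best described as a cheap improvement.

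**What to change.** For women not yet randomized:

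- Add kidney disease, liver disease and clinically significant lung disease to the exclusion list. The sponsor's clinicians should set the severity.
- Move the renal and liver profile, already scheduled at baseline, to the fasting blood draw at screening, and require its review before randomization.
- Apply both to all three arms, so that eligibility does not depend on the assigned treatment.

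Asking for review before allocation while leaving the draw at baseline would not work under the Abstract's sequence, because randomization would then also have to move to after the baseline visit. Moving the draw is simpler.

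The cost is a short amendment, a few more screen failures, and a pre-treatment renal and liver value that is somewhat older when dosing starts. No new test is needed.
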